## Abstract

**Background:**

Malnutrition, with accompanying weight loss, is an unnecessary risk in hospitalised persons and often remains poorly recognised and managed. The study aims to evaluate a hospital-wide multifaceted intervention co-facilitated by clinical nurses and dietitians addressing the nutritional care of patients, particularly those at risk of malnutrition. Using the best available evidence on reducing and preventing unplanned weight loss, the intervention (introducing universal nutritional screening; the provision of oral nutritional supplements; and providing red trays and additional support for patients in need of feeding) will be introduced by local ward teams in a phased way in a large tertiary acute care hospital.

**Methods/Design:**

A pragmatic stepped wedge randomised cluster trial with repeated cross section design will be conducted. The unit of randomisation is the ward, with allocation by a random numbers table. Four groups of wards (n = 6 for three groups, n = 7 for one group) will be randomly allocated to each intervention time point over the trial. Two trained local facilitators (a nurse and dietitian for each group) will introduce the intervention. The primary outcome measure is change in patient’s body weight, secondary patient outcomes are: length of stay, all-cause mortality, discharge destinations, readmission rates and ED presentations. Patient outcomes will be measured on one ward per group, with 20 patients measured per ward per time period by an unblinded researcher. Including baseline, measurements will be conducted at five time periods. Staff perspectives on the context of care will be measured with the Alberta Context Tool.

**Discussion:**

Unplanned and unwanted weight loss in hospital is common. Despite the evidence and growing concern about hospital nutrition there are very few evaluations of system-wide nutritional implementation programs. This project will test the implementation of a nutritional intervention across one hospital system using a staged approach, which will allow sequential rolling out of facilitation and project support. This project is one of the first evidence implementation projects to use the stepped wedge design in acute care and we will therefore be testing the appropriateness of the stepped wedge design to evaluate such interventions.

**Trial registration:**

ACTRN12611000020987

## Background

### Nutritional status of hospitalised patients

The prevalence of malnutrition, defined here as *protein-energy under-nutrition causing measurable adverse effects on tissue/body form and function and clinical outcome*[1] (p. S4), ranges from 20-60% in older patients in Western acute healthcare [1-4]. Additionally, during hospitalisation nutritional status often declines in older patients due to a lack of adequate nutritional intake [5-7]. The adverse clinical outcomes associated with malnutrition and weight loss in acute care include increased: morbidity and mortality, length of stay, rates of infections, pressure sores and readmissions; and decreased functionality [1,8-14]. The economic costs of patient malnutrition and weight loss to healthcare are significant [15,16].

In hospital settings, barriers to preventing nutritional decline have been shown to include a lack of staff knowledge and training [17], lack of prioritisation and timely feeding assistance by nursing staff [18], a lack of coordination between disciplines, including poor interdisciplinary communication, a lack of shared responsibility for nutrition care, and a lack of staff [19]. Naithani, Whelan et al. [20] reported that organisational, environmental and systems issues prevented malnourished patients, or those at risk of malnourishment, from adequately accessing food in the hospital setting. For example, patients were unable to open packaging, missed meals because of scheduled investigatory procedures, were not given food and fluids between mealtimes or these were placed out of reach, and lacked feeding assistance or were interrupted during mealtimes [20].

### Interventions to prevent nutritional decline in hospital patients

The question of how to prevent weight loss and nutritional decline (these terms are used interchangeably in this protocol) in acute patients is complex. Interventions to improve patients’ nutritional status and clinical outcomes have focussed on (i) the use of malnutrition screening tools, (ii) provision of nutritional support including supplements, and (iii) feeding assistance.

Nutritional screening in hospitals is required for accreditation in the US by the Joint Commission (http://www.jointcommission.org), is recommended in the UK by NICE [21] and the British Association for Parenteral and Enteral Nutrition (http://www.bapen.org.uk) and in Australia by the Dietitians Association of Australia as the first step in early detection of at risk patients [1,22]. Typically conducted by nurses [23], the evidence base for improved clinical benefits from screening, and subsequent timely and appropriate referral for nutrition care, is growing [24-26]. However, barriers to implementing nutrition screening tools in clinical practice are commonly encountered; screening rates in hospitals are typically only 60-70% and sometimes much lower [27-31]. A lack of time for what is considered a low priority is commonly cited by nursing staff as a barrier to nutritional screening of patients, additional reasons include lack of training, skills, knowledge and support, patients’ short stays, and a need for enhanced collaboration between dietitians and nurses [27,29,30,32].

Of the large number of available nutritional screening tools [23], the Malnutrition Universal Screening Tool (MUST) developed in 2003 by the British Association for Parenteral and Enteral Nutrition [33] has been widely used [34-37]. The MUST has been shown to be quick (3–5 minutes) and accurate across a variety of hospital patient groups [26,37] and may be completed without weighing patients by using reliable patient or relative memory/recall [26,28]. However, the need for anthropometric measures and the presence of communication difficulties with confused patients are cited as limitations to using MUST [29,30]. Although some studies have claimed it ‘easy’ to use [37], other studies have reported difficulties in using the MUST [30,38].

Nutritional support aims to improve total energy and nutrient intake and may involve provision of oral nutritional supplements (ONS), or, if indicated, enteral tube feeding and/or parenteral nutrition [39]. There are a number of systematic reviews examining the effectiveness of ONS in improving nutritional status and clinical outcomes [5,21,40,41]. Although the review findings are somewhat inconsistent, the evidence suggests that supplementation produces small but consistent weight gain in older people and that improvements in mortality, morbidity (including complication rates) and functional status are greatest in underweight/undernourished patients [5,40,41]. The mean length of stay is not significantly reduced through ONS use [5].

The need for assisted eating is defined as “needing help from another person to be able to eat” ([42], p. 258). Assisted feeding ranges from verbal and non-verbal prompts to physical guiding to transferring food from the plate to an individual’s mouth [43]. Up to 70% of elderly hospital patients require some feeding assistance [44], which is increasingly delivered by patient care assistants as opposed to nurses whose role at mealtimes and responsibilities for patient’s nutritional status has diminished in recent years [18,45,46]. The use of a red tray to identify patients in need of feeding assistance has been advocated across the UK [47-49] and also implemented in a South Australian hospital. Although some studies have shown that nutritional intake can be improved [50,51], the evidence for the effectiveness of feeding assistance in improving patient outcomes is somewhat mixed [43,52,53].

Whilst there is a growing body of scientific evidence for single-faceted nutritional interventions in preventing nutritional decline and, in some cases, improving outcomes of older patients across a discrete sample of hospital wards, there is little research to guide or evaluate the effectiveness of multi-disciplinary, multi-faceted interventions implemented at an organisational level. The study outlined in this protocol aims to redress this imbalance and specifically sets out to address known barriers to implementing evidence about nutrition into clinical practice. Reflecting the focus on improving patient outcomes, the study is titled ‘Prevention and Reduction of Weight Loss in Acute Care (PRoWL)’.

### Specific aims and hypotheses

The study seeks to address four key questions. Firstly, does a multifaceted intervention incorporating a malnutrition screening tool, nutritional supplements and red trays implemented in a hospital improve outcomes for older, at risk patients? Secondly, does the intervention have any impact on staff-related factors (eg receptivity to evidence, staff behaviour and actions) and hospital processes related to nutrition? Thirdly, does the model of facilitated implementation of nutritional evidence support frontline staff to provide evidence-base care? Fourthly, what are the implications for implementing evidence on nutrition within an organisation in terms of successful strategies, sustainability, and study design?

The whole evaluation of the implementation, which will include a stepped wedge design and a full process evaluation of facilitator and staff experiences, will add to existing strategies for implementing nutritional evidence into practice, thereby addressing questions 3 and 4. The following hypotheses that are most pertinent to this study protocol relate to questions 1 and 2 only:

1.1 The multifaceted nutrition intervention will improve outcomes (e.g. prevent nutritional decline, reduce mortality, readmission rates) for older, at risk patients.

2.1 The multifaceted nutrition intervention will improve staff-related outcomes (e.g. receptivity to evidence, staff behaviour).

2.2 The multifaceted nutrition intervention will improve hospital processes related to patient nutrition (e.g. weighing patients, screening patients, documentation).

## Methods/Design

### The intervention

The evidence-based intervention will consist of three linked activities: the introduction and use of the Malnutrition Universal Screening Tool (MUST), the provision of food supplements to patients identified at risk of malnutrition, and the introduction of a system that uses red feeding trays to flag patients requiring full feeding assistance. A multidisciplinary partnership between implementation science researchers (AK, RW, TS), clinicians (AS, LL) and nutrition researchers (SS, IC) was formed to assist in facilitating and evaluating the intervention.

### The implementation

The intervention will be introduced in a staged way across an entire hospital using a stepped wedge design [54,55] described in more detail in the next section. The implementation of the intervention will be facilitated by a nurse paired with a hospital dietitian. The four nurse leads will be identified prior to the project commencing and their wards will be allocated to one of the four groups using stratified randomisation. For three of the four groups an additional five hospital wards will be randomly assigned to the group; the last group will be assigned an additional six wards meaning that a total of 25 wards are allocated (Table 1). Allocation of wards to groups will be conducted (by author TS) by coding each ward and using a random number generator (MS-Excel) to select codes for each groups. The intervention will be implemented over a two month period across all six wards within a group but staggered sequentially every three months between groups. Control sites will experience usual hospital care until the intervention is delivered. The intervention will be carried out over 12 months, commencing in March 2011.

**Table 1 T1:** Representation of stepped wedge trial design showing four groups and five measurement time periods incorporating control (O) and intervention (X) phases

		**Time period**				
		**1**	**2**	**3**	**4**	**5**
Group/Step	1 (six wards)	0	X	X	X	X
	2 (six wards)	0	0	X	X	X
	3 (six wards)	0	0	0	X	X
	4 (seven wards)	0	0	0	0	X

In this trial, 25 hospital wards are randomised to four groups–three groups of six wards and one group of seven wards.

The facilitating nurse-dietitian pairs will be trained in clinical leadership, evidence translation and the intervention (nutritional screening, supplements and the use of red trays prior to the implementation). The structured training available to facilitators will include: a short fellowship at the Joanna Briggs Institute (http://www.joannabriggs.edu.au) to develop evidence implementation and clinical leadership skills, the use of a tool kit containing materials to support their education and leadership roles, and a training pack of clinical content to deliver education to nurses working in their wards. The training materials will be jointly developed with, and facilitators will be supported by, two members of the research team (AK and RW). The clinical content will be developed prior to the roll out by the facilitators working with a dietitian (AS).

The role of the facilitator pairs will be to identify ‘champions’ on each ward and to work with champions to support the roll out of all three components of the intervention before, during and after the intervention phase. The facilitator pairs will train the champions to deliver education and work with champions to undertake unit level audits to determine local compliance with key nutritional evidence-based clinical processes before and after the intervention is implemented, and will assist champions to feed back these local data at each ward.

### Stepped wedge trial

Though infrequently used and poorly known, awareness and use of the stepped wedge trial design is increasing [54,56-58]. Stepped wedge trials are a type of crossover trial in which different groups (or steps) cross over (ie switch from being a control to a treatment) at different time points [59]. In comparison to other crossover trials, the groups/steps only cross in one direction, from control to treatment. The first time point (Time 1) is a baseline measurement, and groups/steps are then randomised to receive the intervention at subsequent time points (Table 1) until all groups/steps have received the intervention [59]. Data is collected from all groups at regular intervals during the study, including at baseline and whenever a new group receives the intervention. At the conclusion of the trial, each of the units in each group have been exposed to the intervention, and each of the groups has a varying amount of control data collected prior to receiving the intervention (Table 1).

A stepped wedge randomised cluster trial with repeated cross section design will be employed [54,55,59]. The ‘step’ refers to each group of wards; and the ‘cluster’ refers to the ward as unit of randomisation. The ‘repeated cross section’ measures refer to the fact that multiple cross sectional measures are made with different patients in each cluster for each of the sampling time periods [55], as recently used in surgical patients across three hospitals [58].

The stepped wedge allows all clusters to receive the intervention. Further, unlike a conventional crossover trial, no clusters are removed from the intervention, which is ethically preferable if there is the prior belief that the intervention should result in benefits for the patient population [54,55,59]. The design also allows for a staged implementation, which is particularly beneficial if there are logistical, practical or financial limitations to rolling out an intervention at all sites in one time period [59]. The design supports evidence implementation in complex, changeable environments because the staged implementation allows improvements to be made to the intervention, for example training materials can be updated to accommodate feedback from participants. Analysis of stepped wedge trials can adjust for possible temporal trends in the effectiveness of the intervention, and the design reduces the impact of intra-cluster correlations on power because each group acts as its own control [54]. A disadvantage of the design is the need for data collection from all units at each sampling period, and potential lengthening of the trial to allow sequential roll out of the intervention across all groups [54]. These attributes support the use of routinely collected hospital administrative data as outcomes of stepped wedge trials.

### The setting

The study will be conducted in a large tertiary South Australian acute care hospital in which patient care areas are divided into six divisions and a total of 26 wards/units. A recent evidence implementation project on nutrition screening and documentation found substantial improvement from low baseline levels in two hospital wards and identified more widespread interest for further improvement to nutritional status and care of vulnerable patients [60,61]. Additionally, a number of internal, unpublished audits have identified that up to half of patients are at risk of nutritional decline in a system that does not prioritise patient nutrition.

### Inclusion and exclusion criteria

Critical care areas will be excluded from the study, all remaining 25 wards will be allocated to one of the four stepped wedge groups. Otherwise, there are no exclusion criteria for implementing the intervention-all nursing staff and patients on the wards will be eligible to be exposed to the intervention. The patients will all be over 18 years of age with no upper age limitation.

### Outcomes

The primary patient outcome measure will be the rate of change in body mass and body mass index over weekly periods from admission to discharge. Body mass (kg) will be measured to the nearest 0.1 kg, between 0800 and 1200 and post bladder voiding. Depending on patient mobility this may require a standing, sitting, bed or sling weighing machine. Patient’s height (cm) will be measured to the nearest 0.1 cm using a stadiometer or predicted from measured ulna length depending on patient mobility. Body mass index (kg/m^2^) is calculated as body weight divided by height squared. The body mass data will be collected by a researcher (LL), who is not blinded to the randomisation schedule.

Secondary patient outcome measures will include: length of stay, all cause mortality, discharge destination (to a higher, lower or equivalent level of care), number and duration of re-admissions (defined as an unplanned admission within 28 days of discharge related to the primary admission [62] (3, 6, 12 months post-discharge), and number of Emergency Department (ED) presentations (3, 6, 12 months post-discharge). The re-admission and ED presentations data will be collected from across all five major public hospitals in the metropolitan region using the State’s patient record systems, which will also provide length of stay, discharge destination and mortality, cross-referenced with State death registries. The collector of the secondary patient outcome data will be blinded to the randomisation schedule.

The staff-related outcome is nurse perspectives of context of care as assessed by administration of the Alberta Context Tool (ACT) [63,64] before the intervention.

Hospital process-related outcomes include: compliance to using the MUST tool on all patients, compliance to using additional food supplements when indicated, compliance to using the red tray system when indicated and compliance to documenting patient’s foods and fluids intake by nurses. The hospital process measures will be obtained through medical record review.

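### Every primary weight is taken by one unblinded researcher from the study partnership; the risk is confined to discretionary steps, its size is unknown, and it is cheap to reduce

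*Protocol article*

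**What the plan says.** The primary outcome is "the rate of change in body mass and body mass index over weekly periods from admission to discharge", so it is built from differences between successive weighings of the same patient. On who takes the readings, the Outcomes section says "The body mass data will be collected by a researcher", and that this is a person "who is not blinded to the randomisation schedule". The abstract repeats it: "with 20 patients measured per ward per time period by an unblinded researcher".

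The section headed The intervention lists the same initials, among the clinicians, in the multidisciplinary partnership that "was formed to assist in facilitating and evaluating the intervention".

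The reading is partly standardised: "Body mass (kg) will be measured to the nearest 0.1 kg, between 0800 and 1200 and post bladder voiding". The device depends on the patient's mobility: "this may require a standing, sitting, bed or sling weighing machine".

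For the other patient outcomes the arrangement is reversed: "The collector of the secondary patient outcome data will be blinded to the randomisation schedule". Those data come from State record systems and death registries.

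**The concern.** The outcome most exposed to the person measuring it has the unblinded assessor, and the outcomes least exposed have the blinded one. This is a stated choice, made twice in the article, and not a detail lost in condensing it.

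Because the outcome is a change score, an offset common to both weighings of a patient cancels. So does an offset common to control and intervention periods. What does not cancel is a follow-up reading treated differently once a ward has crossed over, for example if an unexpected loss is re-weighed more readily in one phase than in the other. Such a shift switches on at crossover in every ward and so follows the 0/X layout of Table 1 exactly. Ward effects and period effects in the planned mixed model cannot separate it from the intervention effect. At stake is a spurious or exaggerated effect in a study whose Discussion expects its results to inform a larger one.

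**Working it through.** **Step 1. Reproduce the plan's own figure, to obtain a trustworthy standard error.**

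Inputs from Sampling, Analysis and Table 1: I = 4 measured wards, T = 5 periods, 20 patients per ward-period, baseline prevalence 0.267, between-ward SD τ = 0.056. From the 0/X layout, U = 10 (intervention cells), W = 30 (sum of squared column totals), V = 30 (sum of squared row totals). Alpha is not stated; two-sided 0.05 reproduces the plan.

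Hussey-Hughes variance, with s² the variance of a ward-period mean:

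Var = I·s²·(s² + T·τ²) / [(I·U − W)·s² + (U² + I·T·U − T·W − I·V)·τ²]

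- s² = 0.267 × 0.733 / 20 = 0.009786; τ² = 0.003136
- numerator = 4 × 0.009786 × (0.009786 + 0.015680) = 0.000997
- denominator = 10 × 0.009786 + 30 × 0.003136 = 0.19194
- SE = √(0.000997 / 0.19194) = 0.0721
- power for 26.7% to 6.5%: Φ(0.202/0.0721 − 1.96) = 80.0% (plan: 80%)
- power for 26.7% to 16.5%: Φ(0.102/0.0721 − 1.96) = 29.3% (plan: 29%)

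**Step 2. Carry the design to continuous weight change.**

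The plan's inputs imply an intraclass correlation of 0.003136 / (0.003136 + 0.195711) = 0.016. Putting s² = (1 − 0.016)/20 and τ² = 0.016 into the same formula gives SE = 0.162 SD. The document gives neither the SD of weekly change nor a correlation for continuous change. I assume SD 1.5-3 kg and vary the correlation over 0-0.05.

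**Step 3. False-positive rate with no true effect and a mean differential shift b in intervention cells.**

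P(reject) = Φ(−1.96 − b/SE) + 1 − Φ(1.96 − b/SE)

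Example, SD 2 kg and b = 0.2 kg: SE = 0.162 × 2 = 0.323, b/SE = 0.619, P = Φ(−2.579) + 1 − Φ(1.341) = 0.005 + 0.090 = 9.5%.

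**Step 4. The same for the binary event.**

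Assume normally distributed change and, as a simplification, the 2 kg cut for all patients (the plan uses 1 kg below BMI 20). Shifted prevalence = Φ(z(0.267) − b/SD), with z(0.267) = −0.622. Example, SD 2 kg and b = 0.3 kg: Φ(−0.772) = 22.0%, a difference of 0.047; divided by 0.0721 this is 0.65, and P = 10.0%.

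| Mean differential shift | Continuous, SD 2 kg, correlation 0.016 | Continuous, full assumed range | Binary, SD 1.5-3 kg |
|---|---|---|---|
| 0.1 kg | 6.1% | 5.4-7.6% | 5.3-6.0% |
| 0.2 kg | 9.5% | 6.8-15.6% | 6.0-9.0% |
| 0.3 kg | 15.3% | 9.1-29.3% | 7.3-13.7% |

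For scale, the difference detectable with 80% power at SD 2 kg is (1.96 + 0.842) × 0.162 × 2 = about 0.9 kg, so 0.2-0.3 kg is roughly a quarter to a third of it.

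**The case against.** The case on the other side is substantial, and much of it stands.

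- **Weight is a displayed number, not a rating.** Resolution, time of day and voiding are fixed, and the choice of machine is tied to mobility and not to the assessor's preference. This stands, and it confines the risk to discretionary steps.
- **The bias is supposed.** No passage describes discretionary re-weighing. The shifts in the table are means over all patients in intervention cells. If only 10% of patients were affected, a 0.2 kg mean would need an error of 0.2/0.10 = 2 kg in each of them, all in one direction. This stands: the table says what a shift would do, not that one will occur.
- **The article is condensed.** Rules on clothing, tare and the layout of the data form may be in a fuller protocol. This stands, and their absence is not held against the plan. The unblinded assessor is different, because the article states it.
- **It is disclosed.** The abstract and Outcomes both say so. But the Discussion mentions difficulty in blinding only in general terms for non-drug trials, and its named limitations are the single site, biochemical markers, power and generalisability.

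Two stronger readings are tempting. A reader might infer that the assessor helps to deliver the intervention and so has a stake in it. The partnership's remit is evaluation as well as facilitation. Ward delivery belongs to nurse-dietitian pairs, supported by two other researchers, and no delivery role is stated for the assessor. A reader might also infer that the trial's error rate is inflated by a known amount. The documents give no shift, no SD and no correlation for weight change, so they do not support that.

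**Conclusion.** The point holds in a limited form. The primary outcome is read by one person who knows each ward's phase and belongs to the study partnership, while blinding is spent on outcomes that hardly need it. Any follow-up shift that differs by phase is inseparable from the treatment effect. How large such a shift might be cannot be learned from the documents. At the scale resolution of 0.1 kg it barely matters (about 5-8%). At 0.2-0.3 kg it would be material (about 7-29% on continuous change, 6-14% on the binary event). These ranges rest on an assumed SD of 1.5-3 kg, an assumed intraclass correlation of 0-0.05 for continuous change, a two-sided 5% test inferred from the power figures, normal change, and a shift present on average across all intervention cells. This is a worthwhile inexpensive improvement, not a defect that invalidates the design.

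**What to change.** Keep the same assessor and change how follow-up weights are recorded:

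1. Enter each follow-up weight on a form that does not show that patient's earlier weights.
2. Set one rule for taking a reading that applies identically in control and intervention periods, with no repeat triggered by comparing the value with the earlier one.
3. Name the unblinded assessment of the primary outcome among the limitations.

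The cost is a revised form and slightly slower weighing sessions; no extra staff are needed. Concealment will be partial. The article describes weighing as routine care and foresees ward weighing on admission and weekly, so earlier values may be on the ward chart. They may be there more often after crossover, since hypothesis 2.2 expects the intervention to improve weighing. Photographing the display or having a blinded person enter the value would protect transcription only, not the decision to re-weigh. Duplicate readings for every bed or sling patient would cost more than the problem clearly warrants. Neither is needed.
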